#### Missing data

Missingness of data might be a concern in research question 3 of study part 1 (the association between person-related variables and existence and validity of advance directives) and in study part 2 (comparison of the frequency of advance directives, valid advance directives, and of the patients’ satisfaction with their existing advance directives during the baseline vs. the intervention phase). In study part 2 (intervention study), we assume that most missing data is created by participants accidentally skipping a question. Therefore, the study person receiving the questionnaires from participants goes through them and asks participants to fill in any missing data. In order to avoid a loss to follow-up, we designed the study follow-up as a low-threshold telephone interview with the additional motivating element that patients can use as a means to contact their treating physician to ask questions concerning their therapy. Therefore, we assume that all missing data will be lost completely at random in the intervention study and that the amount of missing data will be very low so we can obtain unbiased test results from a complete case analysis. In study part 1, however, more missings can be expected because a wider range of participants takes part in the study, particularly those with pronounced deficits that impair answering the questionnaire items. To ensure the best possible data quality, information may be provided by relatives or proxies (e.g., the existence and validity of advance directive). However, this does not apply to questions regarding the participant’s personal opinion (e.g., satisfaction with the advance directive, health literacy, autonomy in medical decision-making). Assuming that cognitive impairment is primarily responsible for the missingness of these data, we include the MMSE score in our model as a mediator variable. Therefore, we expect to obtain unbiased regressors even if the data are only missing at random and not missing completely at random.

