**Fig. 1 Fig1:**
[figure not shown]
Procedure

In both memory clinics, participants with suspected dementia usually undergo three appointments: A medical history interview with the treating physician, a neuropsychological assessment, and an appointment for communicating the diagnosis. Moreover, the memory clinics try to follow-up on every patient, but this has not yet been performed reliably.

The study’s T1 incorporates the three appointments at the memory clinic. At the medical history interview (first appointment), participants consent to the present study (for details regarding informed consent, see below). Moreover, additional person-related variables not collected as part of the standard medical treatment will also be assessed, such as education, need for autonomy in medical decision making, health literacy, and comorbidities.

During the neuropsychological assessment (second appointment), the MMSE score is determined as a marker of cognitive decline and the score of the GDS [9] as a marker of depressive symptoms.

After communication of the diagnosis (third appointment), eligible participants in the intervention phase^1^ are asked whether they want to participate in ACP with the aim of creating an advance directive. If they consent, the study physician will arrange additional appointments besides the usual treatment to perform the ACP.^2^ The number and duration of these vary according to need. If not, a short questionnaire is filled out on the patient’s reasons for rejection.

Participants in the baseline phase^3^ do not receive the offer of ACP and are only contacted at follow-up (T2). For ethical reasons, they will be offered participation in ACP within the next 6 months after their appointments at the clinic (outside the present study).

As a consequence of this study, routine follow-up appointments via phone calls will be established as part of the memory clinic treatment. The primary aim of these follow-ups is to check if patients adhere to their medication or non-medical treatment and are able to handle any upcoming side effects. Moreover, questions from the patients or their caregivers about the diagnosis can be answered through these follow-up calls. For reasons of standardization, these follow-ups (T2) happen three to four weeks after a patient’s last appointment at the clinic.

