The T2 questionnaire of this study records participation, outcome, and, if applicable, reasons for rejection, cancellation, or discontinuation of ACP (see Table 1). Participants will again be handed the advance directive questionnaire (see above). Participants who have not completed the ACP process at the time of the follow-up assessment will refer to a (possible) pre-existing advance directive (see statistical evaluation regarding sensitivity analyses on this topic). In addition, demographic data and the severity of dementia will be recorded. The study physician fills in all the answers known to him from the patient file or the ACP process to minimise the burden on the participants. If participants are not available on the phone at the agreed-upon time, the study physician will call them two more times before considering them lost to T2.

**Table 1 Tab1:** Participation in ACP yes/no, reasons and consequences

Participation in ACP	Reason/result
No,	… because he/she was not offered ACP (*baseline phase*)
	… because he/she declined the offer of ACP
Yes,	… the full ACP process has been performed
	… but the ACP process has not been completed yet
	… but the he/she has cancelled/discontinued the process
	… but it turned out during the ACP process that the patient was unable to consent
Other	(please describe)

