#### Primary outcome advance directive: existence and validity

Information on the existence and validity of the advance directive is collected at T0 in a self-report questionnaire and at T2 in a telephone interview. The closed questions were specifically composed for this study.

First, the existence of an advance directive is recorded (“Do you have an advance directive? Yes/no). This question acts as a filter: If no advance directive is available, none of the subsequent questions follows. If the answer is yes, the validity of the advance directive is assessed.

Since advance directives are highly-sensitive personal data, determining their validity via their content is ethically problematic in our view. One approach, therefore, is to ask whether informed consent was given by the participant when the declaration was drawn up, meaning (1) a patient capable of giving consent, (2) had received adequate information to make an informed decision, and (3) this decision had been voluntary [10]. The respective questions with dichotomous response options (yes/no, supplemented by “don’t know”), can be found in Table 2.

**Table 2 Tab2:** Questions on the validity of the advance directive

	Question
Prerequisite	Has the advance directive been made with a notary, physician or psychotherapist?
Adequate information	Has there been a medical/psychotherapeutic consultation?
	Has there been a notarial consultation?
Capacity to consent	Has your capacity to consent been documented by the physician/psychotherapist or the notary when the advance directive was drawn up?
Voluntariness	Did you create the advance directive voluntarily?

Besides asking about participants’ advance directive, in this questionnaire, we also ask about the existence of a guardianship, a guardianship directive, or a lasting power of attorney.

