#### Informed consent and assent

At the first appointment, participants are informed about the study by the study physician and can discuss any questions or other issues they may have. The physician then obtains written consent if participants agree to take part. Participant information and informed consent form are available on request.

Since participants are suspected of dementia, the capability to consent could be an issue. To support the ability to consent, measures to increase the ability of people with dementia to consent to medical interventions according to the German AWMF S2k guidelines to medical procedures [10] will be used. Patients who cannot consent with the help of these supporting measures are excluded from the study as long as no proxy is available to consent in his/her stead. Nonetheless, consent by proxy still requires each patient’s assent. Visible or audible lack of assent at any point of the study will result in the participant’s withdrawal.

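### The claim that part 2's complete-case test is unbiased rests on an MCAR assumption that the protocol's own reasons do not support

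*Protocol article*

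**What the plan says.** For part 2, the Missing data section of the protocol article states that "we assume that most missing data is created by participants accidentally skipping a question". It adds that returned forms are checked for gaps and that follow-up is an easy telephone contact with the treating physician. From this it draws two conclusions. The first concerns the mechanism: "we assume that all missing data will be lost completely at random in the intervention study". The second concerns the quantity and what it permits: "the amount of missing data will be very low so we can obtain unbiased test results from a complete case analysis". No expected rate is given.

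Other sections describe how the T2 outcome arises or is lost:

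- **Primary outcome section:** existence and validity are collected "at T2 in a telephone interview".
- **Data collection:** if a participant does not answer at the agreed time, the study physician "will call them two more times before considering them lost to T2". To spare the participant, the physician also enters whatever he already knows from the clinic record or from the ACP itself.
- **Data collection, on past practice:** "the memory clinics try to follow-up on every patient, but this has not yet been performed reliably".
- **Informed consent and assent:** "Visible or audible lack of assent at any point of the study will result in the" participant being withdrawn.
- **Non-adherence, retention, and withdrawal:** selective withdrawal is named as a source of bias, and a retention measure is the only response.
- **Statistical methods of evaluation:** the confirmatory test is a two-sample chi-squared test. The one sensitivity analysis named deals with ACP still incomplete at T2, not with missing T2 data.

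**The concern.** The step from few missing values to values missing completely at random does not follow. Checking forms and making the call easy bear on how much is missing, not on who is missing. The mechanisms written into the protocol are unanswered calls, withdrawal without assent, and entry of answers from records, and these are not random by construction.

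The record entry matters most. Someone who completed ACP at the clinic can have a T2 status on record without being reached. Someone who declined ACP, or who was seen in the baseline phase, depends more on answering the phone. If that happens, complete-case deletion removes participants without a valid directive from the intervention-phase denominator more often than participants with one, and the comparison shifts towards ACP. This affects the only confirmatory hypothesis, and no planned analysis would reveal it.

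**Working it through.** **Inputs.** Valid directives 25% (baseline phase) and 50% (intervention phase), with an average of five patients a week (Settings and participants). Each phase lasts 25 weeks, so 5 × 25 = 125 per phase. Alpha is not stated; two-sided 5% is assumed. No missingness rate is given, so a range is shown.

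**Step 1: the plan's own figure.** The protocol states power of about 95%. A patient-level chi-squared test with 125 per phase gives 98.6%. Simulating weekly proportions with a Poisson mean of five patients a week gives 95.0% (t-test) or 95.7% (Wilcoxon). The stated figure is therefore reproduced by a weekly analysis. The inputs 25%, 50% and 125 per phase are carried forward.

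**Step 2: do the stated reasons imply MCAR?**

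| Reason given | What it affects | What it leaves open |
|---|---|---|
| Items skipped by accident, forms checked on return | Item gaps on a form | Whole interviews lost after three failed calls |
| Easy call with access to the physician | Share reached | Whether those reached differ by outcome or phase |
| Call integrated into routine care | Number of withdrawals | Forced withdrawal when assent is lacking |

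None of them makes loss independent of outcome.

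**Step 3: size of bias if ACP completers are always recorded.** Assume that the extra 25 points in the intervention phase are ACP completers whose status is always known. Everyone else, in both phases, is lost with probability m. The baseline proportion stays at 25%. In the intervention phase:

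observed proportion = [0.25 + 0.25(1 − m)] / [0.25 + 0.75(1 − m)]

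- m = 5%: 0.4875 / 0.9625 = 50.6%, bias +0.6 points
- m = 10%: 0.475 / 0.925 = 51.4%, bias +1.4 points
- m = 20%: 0.45 / 0.85 = 52.9%, bias +2.9 points

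**Step 4: type I error.** True rate 25% in both phases, 125 per phase, 40,000 simulated trials per scenario:

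| Loss pattern | Type I error |
|---|---|
| 10% MCAR in both phases | 5.0% |
| Loss differs by phase only (5% vs 20%) | 5.1% |
| Outcome-dependent, identical in both phases | 5.0% |
| Baseline 5% lost; intervention records 98% of valid, 92% of not valid | 5.6% |
| Baseline 10% lost; intervention records 95% vs 85% | 6.6% |
| Baseline 10% lost; intervention records 98% vs 80% | 10.1% |

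Harm needs outcome dependence that differs between phases. The recording probabilities are assumptions, not figures from the protocol.

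**Step 5: how much missing data could overturn the result?** Take an observed 25% versus 50%. Count every missing baseline participant as valid and every missing intervention participant as not valid, with share m missing in each phase:

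p0 = 0.25(1 − m) + m; p1 = 0.50(1 − m); difference = 0.25 − 1.25m

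z = difference / √[p̄(1 − p̄) × 2/125], where p̄ is the mean of p0 and p1

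| m | p0 | p1 | Difference | z |
|---|---|---|---|---|
| 5% | 28.8% | 47.5% | 18.8 points | 3.05 |
| 10% | 32.5% | 45.0% | 12.5 points | 2.03 |
| 15% | 36.3% | 42.5% | 6.2 points | 1.01 |
| 20% | 40.0% | 40.0% | 0 | 0 |

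**The case against.** The protocol does not rely on skipped items alone. It addresses loss to follow-up directly, with a short standardised call three to four weeks after the last appointment. If loss is as low as the authors expect, the bias is well under a point at 5% loss, and even the worst case leaves the planned result clearly significant. That stands, and it limits the point.

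Several stronger readings are tempting but not supported:

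- **ACP completers are never missing.** The text does not say so. Unreachable participants are considered lost, with no stated exception for completers. Step 3 assumes it, so its figures describe the case where record capture is complete.
- **The baseline phase has no comparable source.** The clinic record exists in both phases; only ACP knowledge is specific to the intervention phase. Some statuses that are not valid may also be known from ACP. If a further 10% of intervention participants were known to have no valid directive, the result at m = 20% would be 0.45 / (0.25 + 0.10 + 0.65 × 0.8) = 0.45 / 0.87 = 51.7% rather than 52.9%.
- **The bias is large.** Nothing in the protocol supports 20% to 40% unreachable. Past unreliable follow-up concerns earlier routine, not the new calls.
- **Different completeness by phase invalidates the test.** By itself it does not (step 4). In the model of step 3 there is also no bias if ACP adds no valid directives.
- **Cognition drives loss in part 2.** The protocol says this for part 1. Part 2 excludes severe dementia, so carrying it over is an inference.
- **The handling of research question 3 is invalid.** The plan says "we include the MMSE score in our model as a mediator variable". If missingness depends on MMSE and MMSE is in the model, complete-case logistic regression remains consistent. Only the term mediator is loose.

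Details of imputation may belong in an analysis plan that is not shown. The MCAR assumption, the complete-case set and the claim of unbiasedness are nevertheless fixed in this document.

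**Conclusion.** The point holds in limited form. The protocol claims an unbiased complete-case test in part 2, but its reasons concern the amount of missing data, not its mechanism. Its own procedures make recording that depends on outcome, differently by phase, plausible and likely to favour ACP. Unbiasedness is therefore not guaranteed; a reader should not infer that bias has been shown.

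The size depends on a rate that the protocol does not give. With 25% versus 50% and ACP completers always recorded, the estimate shifts by about half a point to one and a half points at 5% to 10% loss. The planned contrast survives any mechanism up to about 10% missing per phase, and not at 15%. This rests on 125 per phase and a two-sided 5% level.

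**What to change.** - Drop the statement that all part 2 missing data are MCAR and the claim of unbiasedness drawn from it.
- Keep all eligible part 2 participants in the analysis under MAR, for example by multiple imputation of T2 status using phase, clinic, T0 directive status, MMSE and age. All of these are already collected.
- Add a best/worst-case or tipping-point analysis by phase. If anonymisation prevents linking T0 to T2, the bounds still need only counts per phase.
- Report T2 completeness by phase, and whether each outcome came from interview or record. If the source is not already noted on the T2 form, this adds one tick-box.
- Replace the word mediator for MMSE in research question 3 with covariate; nothing else there needs to change.

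The cost is some wording, a little programming and slightly wider or less favourable results. As a guide, the crudest all-participant analysis counts missing as no valid directive in both phases. Under equal random loss it gives power of 97.9%, 96.8% and 93.7% at 5%, 10% and 20% missing, against 98.2%, 97.6% and 96.0% for complete cases.

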### Quality control

#### Data management

The Data Management Committee (DMC) is composed of a biostatician and a data manager, both not involved in data collection.^6^ It gives statistical advice, is responsible for data digitalisation, data quality assurance and privacy protection, and surveys the database. All the data will be recorded paper-based. Data relevant for patient treatment will be added to the electronic patient file. The online survey tool LimeSurvey will be used as a database.

The DMC is also responsible for data monitoring, focusing on aspects like missing or implausible values, and value distribution, thereby ensuring data quality. Double data entry is performed on one randomly selected record out of each set of ten successive records by a second person, using algorithms to assess the quality of the entered data. Detected discrepancies will lead to repeated data entry of each of the 10 records. After successful completion of the data entry process, paper-based records will be destroyed.

Since participants are exposed to only very minor risks during the study (see below), no interim analyses during the data assessment phase are planned.

#### Trial monitoring

A Trial Management Committee (TMC) elaborates the details of the study design and procedure and issues the data assessment and the informed consent materials. It meets on a weekly basis to monitor the progress of the study, initiate the next steps, report problems, and agree on solutions. Part of the TMC is a Steering Committee (SC) that oversees the whole trial. It reviews the progress of the study together with the DMC and, if necessary, agrees on changes to the protocol to facilitate the smooth running of the study. The SC keeps the study protocol and the entry to the study registry up to date and, if necessary, communicates amendments to all study members and the ethical review boards (as soon as possible), cooperating partners (quarterly), and the patient advisory board (see below; at its subsequent meeting). It also organizes meetings of the TMC.

#### Principal and lead investigators

The principal investigator designed the study and acquired the grant. She is responsible for the trial initiation and management (head of SC) and takes all the final decisions. It is mainly her who communicates with the associated partners.

Lead investigators are the respective study physician and neuropsychologist at each of the study centres, two leading investigators per centre. They are part of the TMC and form the link between researchers at the University and practitioners in the memory clinics by instructing and continuously informing the other investigators. Moreover, they enrol the patients and collect the study data. Finally, they are responsible for reporting any adverse events as reported by the participants or as observed by themselves back to the TMC.

Principal and lead investigators declare to have no competing interests.

#### Audits

We have installed an ethical advisory board for this study, not related to the University of Siegen as study sponsor, nor to any of our cooperating partners. Members of the Institute for Medical Ethics and History of Medicine at the Ruhr-University Bochum, Germany, will advise us on questions related to research ethics in bi-annual meetings, particularly regarding the problem of involving non-competent persons in research.

Scientific advice will come from international experts of different disciplines. We plan to conduct bi-annual expert workshops on research ethics, assessment of capacity to complete advance directives, and decision-making and task complexity, amongst others. Moreover, the theoretical input on the gerontological concepts of ageing-well will come from the cooperating Frankfurt Forum of Interdisciplinary Ageing Research.

Finally, we have established a patient advisory board at our Institute^7^ that will also be involved in the current study. The general aim of this advisory board is to inform and counsel researchers on practical and ethical questions arising during the research process. This will also allow our research to be closely adapted to the needs of PwAD and their caregivers. Presently, the patient advisory board consists of four patients who meet on a monthly basis. The participating patients receive written information about the next session’s topics beforehand if available. A member of the research group will present the current state of the study and asks the researchers’ questions for the members of the board to discuss. In the current study, besides considering ethical topics when they arise, questions will centre around ACP and expectations regarding its facilitation. This is aimed at gaining a deeper and broader understanding of the needs of PwAD with respect to ACP in preparation for a subsequent study.

### Ethics and dissemination

The study procedure and materials have been reviewed and approved by the Ethics Committee of the Medical Council Westfalen-Lippe and the Medical Faculty of the Westfälischen Wilhelms-Universität Münster, Germany, (trial no. 2021-518-f-S) and the Ethical Committee of the Medical Faculty at the Goethe University Frankfurt am Main (trial no. 2021-559). The study has been registered with the Germany Registry for Clinical Trials (DRKS, Deutsches Register Klinischer Studien, no. DRKS00026691). For interested readers, all items of the WHO Trial Registration Data Set can be found in “Appendix B”.

Any relevant amendments to this protocol will be communicated formally to both ethical committees for approval and to the study registry.

